### Interventions

(See Figure 1)

### Acupuncture (experimental group): 3 sessions (once weekly)

Once a week, before the physiotherapy session, the doctors responsible for the treatment (specialists who are well-acquainted with the technique) will apply acupuncture at the Tiaokou ST38 point, following the *tiao-shan *homolateral technique. This consists of the perpendicular insertion of a single-use sterile filiform acupuncture needle, 7.5 cm long, 30 gauge body diameter, using a guide-tube. The insertion is to be made, after sterilising the skin and with the patient in a prone position, at the Tiaokou point (located equidistally from the flexion fold of the knee and the vertex of the lateral malleolus and 1 inch laterally from the tibial crest, to a depth of 4.5 – 5.0 cm, towards the Chengshan UB57 point (located on the rear surface of the leg, half way between the popliteo fold and the heel, in an inverted-V shaped crease separating the cords of the external calf. Insertion of the needle is followed by vigorous stimulation by means of broad bidirectional rotation movements of the body of the needle, intended to produce the sensation known as Deqi, often described as one of irradiance. The needle is maintained in place for 20 minutes, and manipulated for 1 minute every 5 minutes (i.e. 4 manipulations per session). While the needle is being manipulated, the patient should perform abduction and external and internal rotation exercises.

The single-use sterile needles are manufactured by Cloud & Dragaon Radical Device Co., Ltd (Wujiang, China), according to EU norms, and are imported by Acupuncture Shop, [name].

### TENS placebo (control group): three sessions (once weekly)

Once a week, before the physiotherapy session, the doctors responsible for the treatment will apply the TENS placebo, which consists of placing two adhesive electrodes, one each on the front and rear surfaces of the leg that is homolateral to the affected shoulder. The electrodes are connected to a deactivated TENS apparatus, model 8016 M. The stimulation unit remains placed in front of the patient, such that the flashing of the diode simulating the stimulus is visible at all times. The patient remains in the same position for 20 minutes, after which the TENS unit is disconnected and the electrodes removed from the patient's body. The frequency of the sessions is the same as that for acupuncture.

### Physiotherapy (experimental and control groups): 15 sessions (3 weeks)

The physiotherapy sessions last 40 minutes each and consist of the following (see Additional file 1 1 – Physiotherapy protocol [ISRCTN28687220]):

• Superficial heat therapy (graduated according to the patient's sensations; 5 minutes)

• Recentering of the humeral head (active manoeuvres: 5 minutes; passive manoeuvres: 5 minutes)

• Diadynamic currents, diphase attached with positive pole at the point of greatest pain (graduated according to the patient's sensations; 5 minutes)

• Post-session cryotherapy (10 minutes).

The patient is recommended to avoid any activity that may cause pain in the affected arm for the duration of the study. Ultrasound therapy was not included as an applicable technique because it has been shown to be ineffective in treating pathologies in this region [4].

The daily physiotherapy sessions will follow those of acupuncture and the TENS placebo in the following way: first, a session of acupuncture or TENS placebo followed by the first one of physiotherapy; the next four sessions of physiotherapy to be applied on following consecutive days. The second acupuncture or TENS placebo session is applied prior to the sixth one of physiotherapy, and is followed by another four physiotherapy sessions during the next four consecutive days. The third and final acupuncture or TENS placebo session is applied prior to the eleventh one of physiotherapy, and is followed by another four physiotherapy sessions during the next four consecutive days, after which the final assessment is made. The acupuncture and the TENS placebo sessions take place in identical rooms.

### Rescue medication

The patients are allowed to take analgesics and/or NSAIDs if they wish. If they do, this fact, and the daily dose taken, should be recorded in the digital data record (DDR).

• Anti-inflammatory medication

• If taken, the maximum dose allowed is 1 diclophenac pill (50 mg) three times a day for a maximum of 4 weeks.

• Administration instructions: to be taken with meals, to alleviate possible gastric irritation.

• Gastroprotective medication

• Specific indications:

• No past record of ulcers or risk factors such as anticoagulant therapy, association with corticoids, age > 60 years or severe baseline illness (kidney insufficiency, cirrhosis, COPD): NO GASTROPROTECTION

• No past record of ulcers and risk factors such as anticoagulant therapy, association with corticoids, age > 60 years or severe baseline illness (kidney insufficiency, cirrhosis, COPD): GASTROPROTECTION with 200 μg misoprostol every 6 or 12 hours or 20 mg famitidine every 12 hours.

• Past record of ulcers: GASTROPROTECTION with 20 mg omeprazole every 24 hours.

• Contraindications: diclophenac should not be taken by patients allergic to it, to acetylsalicylic acid or other NSAIDs, by patients with a history of asthma, angiodema or rhinitis provoked by NSAIDs, by patients affected by porphyria or with a history of ulcers, coagulation pathologies or haemorrhages. Caution is advised for patients with kidney insufficiency, cardiac insufficiency, hypertension or liver insufficiency.

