### Selection criteria

Inclusion criteria

• Patients with a clinical diagnosis of subacromial syndrome (rotator cuff tendinitis and subacromial bursitis) with a case history > 3 months

• Prior radiography, with normal results

• Informed consent

• Unilateral injury

Exclusion criteria: surgery, luxations or fractures in the proximity of the shoulder; other severe direct or indirect traumas (in traction) observed in the anamnesis and clearly related to the onset of the current episode; hypocoagulates, generalised disorders of the musculoskeletal system or neurologic disorders, vascular trophic disorders in the lower limbs, lymphedema.

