### Secondary variables

After the first week of treatment, the level of confidence in the treatment is measured on a Treatment Credibility Scale (TCS) [23]. This was first proposed by Borkovec and Nau [24] and comprised four items that are assessed on a continuous VAS from 0 to 10 (0 totally disagree; 10 totally agree). The following elements are included, but at the baseline interview, only the first two questions are asked:

1. Are you confident this treatment will alleviate the pain you feel?

2. Does the treatment seem a logical one?

3. Would you recommend this treatment to a friend or relative who had the same problem?

4. Do you think this treatment could be applied to other problems?

After three weeks of treatment (T-1) (15 sessions of physiotherapy), the following secondary variables will be assessed by an independent evaluator:

• Pain intensity in the shoulder during the day, on a 10 cm VAS (DPI-VAS)

• Pain intensity in the shoulder during the night, on a 10 cm VAS (NPI-VAS)

• Degree of improvement perceived by the patient (IPP) (7 point Likert categoric scale: 0 much worse; 1 worse; 2 slightly worse; 3 no change; 4 slightly better; 5 better; 6 much better) [25]

• Degree of improvement perceived by the evaluator (IPE) (7 point Likert categoric scale: 0 much worse; 1 worse; 2 slightly worse; 3 no change; 4 slightly better; 5 better; 6 much better)

• NSAIDs taken (NT)

• Treatment Credibility Scale items 3 and 4

• Adverse events (ADEV) of a traumatic nature that might distort the results of the evaluation.

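### The rescue-medication rules provide gastroprotection for patients with past ulcers on the anti-inflammatory, then bar patients with a history of ulcers from diclofenac, the only anti-inflammatory named

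*Protocol article*

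**What the plan says.** All the rules at issue are in the protocol article, under Methods/design.

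- **Access to rescue.** The Rescue medication section opens with a general permission: "The patients are allowed to take analgesics and/or NSAIDs if they wish".
- **The drug.** Only one anti-inflammatory is named or given a limit: "If taken, the maximum dose allowed is 1 diclophenac pill (50 mg) three times a day for a maximum of 4 weeks".
- **Gastroprotection.** Three branches follow. Two are for patients without past ulcers, split by whether other risk factors are present. The third is "Past record of ulcers: GASTROPROTECTION with 20 mg omeprazole every 24 hours".
- **Contraindications.** The last bullet states that "diclophenac should not be taken by patients allergic to it, to acetylsalicylic acid or other NSAIDs". It goes on to list further groups who should not take it, and these include patients "by patients affected by porphyria or with a history of ulcers, coagulation pathologies or haemorrhages".
- **Eligibility.** The exclusion criteria in Selection criteria cover shoulder surgery and trauma, and then "hypocoagulates, generalised disorders of the musculoskeletal system or neurologic disorders, vascular trophic disorders in the lower limbs, lymphedema". Ulcer history does not appear.
- **Outcome.** NSAID intake is a secondary variable at the end of treatment and at each follow-up.

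**The concern.** Two bullets in the same section deal with the same patients and point in different directions. The gastroprotection branch treats a past ulcer as a reason to add a protective drug, so it assumes that the anti-inflammatory is taken. The contraindication treats a past ulcer as a reason not to take diclofenac at all.

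What is at stake is first a safety instruction on gastrointestinal risk. A doctor who allows diclofenac with the protective drug and a doctor who refuses diclofenac can both point to the protocol. The second consequence is smaller: if centres settle the matter differently, part of the recorded NSAID intake reflects each centre's reading of the rule. The article's own Discussion names loss of uniform judgement between researchers as a risk of the multicentre design.

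**Working it through.** No arithmetic applies. The point rests on two stated rules and does not depend on alpha, power, effect size, standard deviation or dropout. The check is to set the rules side by side and see whether any other text reconciles them.

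1. **Does the ulcer branch presuppose use of the anti-inflammatory?** It is the third branch of a scheme that comes directly after the diclofenac dose limit. The other two branches decide whether someone taking the anti-inflammatory needs protection. Within these rules the third branch has a purpose only if patients with past ulcers also take it.

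2. **Which drug is meant?** The opening permission covers analgesics and NSAIDs in general, but diclofenac is the only NSAID named or dosed. The ulcer branch names no other.

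3. **Is the contraindication qualified?** "by patients affected by porphyria or with a history of ulcers, coagulation pathologies or haemorrhages" carries no restriction to active, recent or complicated ulcers, and no exception for patients given gastroprotection. The same bullet has a separate, weaker tier that asks only for caution, for certain kidney, heart, liver and blood-pressure conditions. Ulcer history is in the prohibition tier, so the bullet cannot be read as permitting use with protection.

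4. **Can such patients enter the trial?** Yes. Ulcer history is absent from the exclusion criteria, so the conflict can arise in an enrolled patient.

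5. **Does other text resolve it?** No other section of the article returns to ulcer history or says which bullet takes precedence.

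6. **Would the data show who was affected?** Not from the items listed. The daily rescue dose is to be recorded, but the Baseline assessment (T-0) list has no item for ulcer history.

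| Patient with past ulcers who wants an anti-inflammatory | Gastroprotection bullet | Contraindication bullet |
|---|---|---|
| Diclofenac | presupposed, with a protective drug | not to be taken |
| Another NSAID | none named | not addressed |

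**The case against.** The strongest defence is that the two bullets do not collide word for word. The ulcer branch does not mention diclofenac, the opening sentence permits NSAIDs generally, and the contraindication covers diclofenac alone. A centre that withheld diclofenac and gave gastroprotection alongside a different NSAID would breach neither sentence. This stands to a limited extent: the accurate description is that the bullets conflict as written and need clarification, not that compliance with both is logically impossible. It does not remove the problem, because the text names no other NSAID and does not say that the branch is meant for one. A centre would have to supply that rule itself.

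A second defence is that a journal article condenses a fuller protocol. That excuses omissions. Here both instructions are stated, and they disagree.

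A third is that the rule is the same in both arms and that each centre randomises its own patients, so differences between centres are not in themselves differences between arms. This stands, and it limits the point to safety and uniform handling.

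A reader might also infer a second contradiction over anticoagulation, since that therapy is listed as a gastric risk factor while "hypocoagulates, generalised disorders of the musculoskeletal system or neurologic disorders" are excluded. The documents do not support this. If the exclusion covers anticoagulated patients, the risk-factor entry is merely redundant. If it does not, there is no conflict with eligibility. The contraindication concerns coagulation pathologies, which the text does not equate with anticoagulant therapy.

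**Conclusion.** The inconsistency is real and confined to the Rescue medication section. It matters because it is a patient-safety instruction that can be followed in opposite ways. It may also make NSAID intake, a secondary variable, less uniform across centres.

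Its size in patients cannot be given. The article states no frequency of ulcer history, and any percentage applied to the planned 465 would have no basis in it. Rescue medication is optional, so only patients with past ulcers who would take an anti-inflammatory meet the conflict in practice.

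A reader might infer that the inconsistency biases the pain or Constant scores. The documents do not show this. The rule is common to both arms, and nothing in the text describes a way in which it would be applied differently between them. The sample size does not depend on it, and no effect on the primary comparison is shown.

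The conclusion rests on one reading: that the ulcer branch refers to the anti-inflammatory named just before it. The structure of the section supports that reading, and the text offers no alternative.

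**What to change.** The clinical investigators should reconcile the ulcer branch of the gastroprotection scheme with the contraindication bullet, so that one rule covers patients with a history of ulcers. The rule should also say whether it concerns diclofenac only or any NSAID. It should then go to every centre in the same wording. Which rule is right is a clinical decision, and no view is taken here.

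The cost is a short amendment or clarification letter. The article describes recruitment as still open, so the letter could reach centres while it still matters.

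A check in the digital data record is optional. The system already has obligatory fields and validation rules, but the check would need ulcer history as a new baseline item as well as the validation rule. That field would also let the analysts count the patients concerned.

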### Study variables

#### Baseline assessment (T-0)

For the sake of consistency, criteria of selective tension and mobility patterns [22]that we believe are clear enough for homogeneous diagnoses to be achieved (see Additional file 2) will be applied. When the patient has been diagnosed, he/she will be invited to give informed consent to take part in the study. If this is received, the initial assessment will be made by an external rehabilitation evaluator, who will record the following data:

• Sociodemographic data

• Age

• Sex

• Influence on the shoulder of the type of work performed (no effect, moderate effect, severe effect)

• Background

• Previous episodes of shoulder pain (number of episodes)

• If previous episodes occurred, did they provoke sick leave? (No. of such events and their duration)

• Current episode

• Concomitant neck pain(yes/no)

• Duration of the present episode (in months)

• Previous treatment received for the same episode (corticoid injections, analgesic or anti-inflammatory medication)

• Acute onset of the present episode (yes/no)

• Direct cause (excessive tension or otherwise, slight injury or unknown cause)

• Is the affected shoulder the dominant one? (yes/no)

• Constant's Shoulder Function Assessment (SFA) Scale

• Pain intensity in the shoulder during the day, on a 10 cm Visual Analogue Scale (VAS)

• Pain intensity in the shoulder during the night, on a 10 cm Visual Analogue Scale (VAS)

• Analgesic and NSAID medication taken during the previous 2 weeks (4 point Likert scale: 0 no medication; 1 less than the usual daily dose; 2 the normal dose; 3 more than the normal dose).

### Main result variable (endpoint)

At 3 weeks (T-1) after the start of the study, the results of the intervention will be assessed by an independent expert evaluator. The 3-month follow up will be performed by the same evaluator. An additional follow up will be carried out at 6 and 12 months after the final evaluation (by independent telephone interviewer), including the main result measurements. These are the change in the SFA score, with respect to baseline values, after the 15th physiotherapy session. This assessment will be made by an external rehabilitation specialist with no information regarding the treatment received by the patient. Constant's Shoulder Function Assessment (SFA) Scale has a maximum score of 100 points, including subjective and objective elements in a proportion of 35/65, respectively. The subjective parameters describe the degree of pain felt by the patient and his/her ability to carry out normal daily activities, as regards both the level of activity and the position of the arm. The objective parameters are based on the range of active compound movements that enable the arm to be moved to functionally relevant positions, using a goniometer to measure the rear and lateral elevation and the positioning of the hand in relation to the head and the trunk in order to assess the degree of rotation achieved. The score for the power exerted by the shoulder is based on the weight (in kg) the patient can raise in abduction, to a maximum of 11 kg. A total SFA score of 100 indicates a shoulder with perfect freedom of movement, no pain and normal functioning.

### Secondary variables

After the first week of treatment, the level of confidence in the treatment is measured on a Treatment Credibility Scale (TCS) [23]. This was first proposed by Borkovec and Nau [24] and comprised four items that are assessed on a continuous VAS from 0 to 10 (0 totally disagree; 10 totally agree). The following elements are included, but at the baseline interview, only the first two questions are asked:

1. Are you confident this treatment will alleviate the pain you feel?

2. Does the treatment seem a logical one?

3. Would you recommend this treatment to a friend or relative who had the same problem?

4. Do you think this treatment could be applied to other problems?

After three weeks of treatment (T-1) (15 sessions of physiotherapy), the following secondary variables will be assessed by an independent evaluator:

• Pain intensity in the shoulder during the day, on a 10 cm VAS (DPI-VAS)

• Pain intensity in the shoulder during the night, on a 10 cm VAS (NPI-VAS)

• Degree of improvement perceived by the patient (IPP) (7 point Likert categoric scale: 0 much worse; 1 worse; 2 slightly worse; 3 no change; 4 slightly better; 5 better; 6 much better) [25]

• Degree of improvement perceived by the evaluator (IPE) (7 point Likert categoric scale: 0 much worse; 1 worse; 2 slightly worse; 3 no change; 4 slightly better; 5 better; 6 much better)

• NSAIDs taken (NT)

• Treatment Credibility Scale items 3 and 4

• Adverse events (ADEV) of a traumatic nature that might distort the results of the evaluation.

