The placebo selected differs considerably from the acupuncture technique under study, but the intervention in itself is, in fact, difficult to disguise [27]. The depth of needle insertion and the manipulations subsequently effected prevent the use of placebos that are totally credible [28]. This is why we decided to apply an inactive control treatment (the TENS placebo), in order to subject the two groups of patients to the same rhythm of intervention. Nevertheless, the degree of credibility of the intervention and of the placebo will be assessed at the start and at the end of the study. This type of control was first used experimentally by Macdonald [29]. The placebo effect is related to the patient's expectation, to the observer and to the doctor's attention, in combination with classical Pavlovian-type response conditioning activated by the positive or negative expectation of a cure. Petrie and Hazleman [30]used a scale to measure the credibility of acupuncture treatment and that of the TENS placebo, and reached the conclusion that both methods were equally credible, thus justifying the use of the TENS placebo as a control.

Although the characteristics of the intervention prevent us from establishing a double blind design, we intend to blind the patients from the evaluator, and believe this simple blinding will make it possible to achieve sufficient control of possible bias.

As with any other multicentre study, we are confronted with certain disadvantages, such as the loss of unity of judgement, with the participation of various researchers, or the reduced homogeneity of the sample group and the parallel increase in data dispersion. In order to overcome these problems, we have had to create very simple criteria for patient selection, to avoid possible subjectivity as concerns the different researchers. Additionally, we have laid great stress on the need to obtain a good level of communication between the different work groups, a condition that is sometimes essential to standardise criteria and to guarantee the internal validity of the study. The best way to achieve this communication is by means of frequent meetings, the coordination of which will be the responsibility of the study controller.

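### The evaluator whose blinding protects the outcomes is also assigned to collect credibility ratings of the treatment at T-1, and the credibility schedule is inconsistent across sections

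*Protocol article*

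**What the plan says.** All references are to the protocol article.

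- **Secondary variables, T-1 list.** The list opens: "After three weeks of treatment (T-1) (15 sessions of physiotherapy), the following secondary variables will be assessed by an independent evaluator". It includes improvement as judged by the evaluator (IPE) and "Treatment Credibility Scale items 3 and 4". Item 3 is "Would you recommend this treatment to a friend or relative who had the same problem" and item 4 is "Do you think this treatment could be applied to other problems". All items are rated on a 0 to 10 visual analogue scale.
- **Main result variable (endpoint).** The SFA at T-1 is scored by an independent specialist "with no information regarding the treatment received by the patient". The same evaluator carries out the 3-month follow-up.
- **Randomisation.** The treatment code is hidden from the evaluator. Of the three PDA users, only the treating doctor can see it.
- **Discussion.** A double-blind design is said to be unattainable, and keeping the evaluator blind is presented as the means of controlling bias. It adds that "the degree of credibility of the intervention and of the placebo will be assessed at the start and at the end of the study".
- **Timing of the credibility scale.** Secondary variables first places the scale after week 1 of treatment, then says "but at the baseline interview, only the first two questions are asked", and then puts items 3 and 4 at T-1. The T-0 list under Baseline assessment contains no credibility item.

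**The concern.** The two treatments cannot be mistaken for each other. One is a manipulated needle in the leg; the other is a pair of electrodes and a unit with a flashing diode. Patients were also told about the techniques. A patient asked whether they would recommend the treatment, or see it used for other problems, may easily name it. The protocol hides the treatment code from the evaluator and then gives that evaluator a task that turns the patient's attention to the treatment, at the visit where the primary outcome is measured.

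The outcomes exposed are those in which judgement enters: IPE entirely, and the SFA to the extent that 35 of its 100 points are subjective and the rest depends on how movement and strength are measured. Because the same evaluator returns at 3 months, anything learned at T-1 could affect the SFA and IPE at that visit too.

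A second, separate problem is that the credibility data are meant to support the choice of TENS placebo as control, but the schedule cannot be read in one way only.

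**Working it through.** **1. Who collects what at T-1.** The plan gives no figure on this point, so the check is a comparison of sections.

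| Task at T-1 | Person named | Section |
|---|---|---|
| SFA (primary) | independent expert evaluator, blind to treatment | Main result variable |
| IPE | independent evaluator | Secondary variables |
| Credibility items 3 and 4 | independent evaluator (same sentence and list as IPE) | Secondary variables |

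For IPE and the credibility items the overlap is explicit, since one sentence governs both. That the SFA assessor is the same person is the natural reading, but it is not stated. The article names no other collector for the items and gives no order within the visit.

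**2. Which items are asked when.** Secondary variables allows two readings.

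| | Baseline interview | After week 1 | T-1 | Baseline and T-1 share | Any early time and T-1 share |
|---|---|---|---|---|---|
| Reading A: the week-1 interview is the baseline interview | (same as week 1) | 1, 2 | 3, 4 | none | none |
| Reading B: two separate occasions, full scale at week 1 | 1, 2 | 1, 2, 3, 4 | 3, 4 | none | 3, 4 |

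Under both readings the baseline interview and T-1 have no item in common. Only under Reading A is no item repeated at all. If baseline means T-0, the T-0 list omits the scale, and items 1 and 2 would be asked before any treatment had been given.

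**3. Illustration of what evaluator bias could do.** Inputs from Sample size and associated power: SDs 17 and 18, planned means 70 and 65, 226 and 239 patients, 20% dropout.

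- Completers: 226 × 0.8 = 180.8, about 181; 239 × 0.8 = 191.2, about 191.
- SE of the difference = √(17²/181 + 18²/191) = √(1.597 + 1.696) = 1.815.
- With no true effect and an average between-arm shift b, type I error = P(|Z + b/SE| > 1.96).
- b = 1 (assumed): b/SE = 0.55; type I error about 0.085. The shift is 1/5 = 20% of the planned 5-point difference.
- b = 2 (assumed): b/SE = 1.10; type I error about 0.197.

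Here b is an average over all patients. If a fraction p disclose and the between-arm shift among them is d, then b = p × d. For example, b = 1 with a quarter disclosing (assumed) needs d = 4 points. The document gives neither p nor d.

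**The case against.** The strongest reply is that unblinding here is conjecture. Items 3 and 4 name no modality, a mark on a visual analogue scale requires no description of what was done, and the same visit already covers patient-rated improvement, NSAID use and adverse events, any of which could prompt a disclosure. This stands in part: the items reveal nothing by themselves, and their added risk over the rest of the visit cannot be quantified. They are nevertheless the only entries in that list that ask the patient to judge the treatment itself rather than the patient's condition, medication or events.

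It may also be said that form handling and visit order belong in the full protocol. That would answer a complaint about missing detail. The point here is what the article does state: it gives the items to the evaluator.

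Four stronger inferences are tempting, and the document does not support them:

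- *That this is the trial's only blind.* The Abstract and Design also specify a blind, independent analysis. Evaluator blinding is the main safeguard of outcome measurement, not the sole blind.
- *That no item is taken both early and late, or that no four-item score ever exists.* This holds under Reading A only.
- *That credibility cannot be compared between arms.* It can, at every time and on whichever items are asked. The Discussion promises assessment at two times and does not expressly promise within-item change.
- *That the type I error figures measure the effect of these two items.* They show what evaluator bias of an assumed size would do, whatever its source.

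**Conclusion.** The point holds as an avoidable risk and an internal inconsistency. The protocol assigns two questions about the treatment to the evaluator who rates IPE and, on the natural reading, scores the primary SFA. It does so in a design that relies on that evaluator's ignorance of the arm, and with the same evaluator returning at 3 months. No break of the blind is shown, and its likelihood cannot be estimated from the document. The figures of about 8.5% and 20% rest wholly on the assumed shifts of 1 and 2 points.

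Separately, Baseline assessment, Secondary variables and the Discussion do not give one consistent credibility schedule. The firm consequence is limited: no item can be followed from the baseline interview to T-1. Because the risk falls on the primary outcome and is cheap to remove, the change should be made, but this is not a flaw that invalidates the design.

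**What to change.** 1. Remove the Treatment Credibility Scale from the evaluator's T-1 list. Have patients complete it on a form returned to staff other than the evaluator, after SFA and IPE have been locked in the PDA. Data collection and analysis already makes approved evaluation records uneditable, so the scale would need its own record, entered under an access code other than the evaluator's.
2. Ask the same four items at one early post-treatment time and again at T-1, so that between-arm comparison at each time and same-item change are both available.
3. Reconcile Baseline assessment, Secondary variables and the Discussion: state whether the first administration is at T-0 or after treatment has begun, which items it contains, and what the start and the end of the study mean for this scale.

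Cost: a changed form, a fixed order within the T-1 visit, and a few extra visual analogue items per patient. No extra visits are needed, and existing staff can receive the forms.
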